### Data management and confidentiality

All study data will be entered into a secure, access-controlled database using unique participant identifiers. Identifiable information will be stored separately from research data. Range checks, double-checking of critical variables, and audit trails will be used to improve data quality. Access will be restricted to approved study personnel.

Robot interaction logs, transcripts, audio-derived features, task performance data, MRI data, and biomarker data will be stored according to institutional requirements and the approved ethics protocol. Data sharing will follow participant consent, local data protection regulations, and Frontiers data availability requirements. De-identified data and analytic code may be made available upon reasonable request when ethically and legally permissible.

### Statistical analysis

Analyses will follow a prespecified statistical analysis plan finalized before database lock. The primary analysis will follow the intention-to-treat principle and include all randomized participants with available outcome data. A per-protocol sensitivity analysis will include participants who complete at least 80% of scheduled sessions (at least 58 of 72 sessions) and complete the week 24 primary outcome assessment.

Baseline demographic and clinical characteristics will be summarized using descriptive statistics. Continuous variables will be reported as mean and standard deviation or median and interquartile range, depending on distribution. Categorical variables will be reported as counts and percentages. Baseline comparability will be described rather than used as a basis for post-randomization exclusions.

The primary endpoint will be analyzed using a linear mixed-effects model with fixed effects for group, time, and group × time interaction, and with participant-level random effects to account for repeated measures. The primary contrast will be the adjusted between-group difference in MoCA change from baseline to week 24. Week 36 data will be included in durability models to estimate maintenance or decay of intervention effects after training completion. Age, sex, education level, and baseline cognitive severity will be included as covariates when prespecified. Effect estimates will be reported with 95% confidence intervals and *p* values.

Secondary continuous outcomes will be analyzed using linear mixed-effects models or generalized linear mixed models as appropriate. Binary or count outcomes such as completion status, adverse events, and help requests will be analyzed using generalized models with appropriate link functions. Missing data will be handled under the missing-at-random assumption in mixed models, with multiple-imputation sensitivity analyses considered if missingness is substantial or differs by group. The single primary endpoint will be tested at a two-sided alpha level of 0.05. Secondary outcome families will be interpreted with control of multiplicity using the Benjamini-Hochberg false-discovery-rate procedure within prespecified families, including cognitive secondary outcomes, emotional/motivational outcomes, engagement/usability outcomes, and safety outcomes; unadjusted and adjusted q values will be reported.

For rs-fMRI outcomes, ROI-to-ROI connectivity changes will be analyzed using within-group and between-group models. Whole-brain voxelwise analyses will use correction for multiple comparisons, such as false discovery rate or cluster-level family-wise-error correction. Biomarker changes will be analyzed using mixed-effects models or non-parametric alternatives if assumptions are not met, with false-discovery-rate correction across biomarker panels. Associations between changes in neurobiological measures and cognitive outcomes will be explored using Pearson or Spearman correlations and multivariable regression as appropriate, with clear labeling as exploratory.

All statistical tests will be two-tailed. Statistical significance for the primary endpoint will be set at *p* < 0.05. Secondary, week 36 exploratory durability, and imaging-biomarker analyses will be interpreted according to their prespecified exploratory or confirmatory status, with emphasis on effect sizes, standardized beta coefficients, or partial eta-squared values and 95% confidence intervals rather than *p* values alone.

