### Neuroimaging and biomarker sub-cohort

A nested exploratory imaging-biomarker sub-cohort of approximately 50 participants (target 25 per group), subject to MRI eligibility, consent, and feasibility, will undergo rs-fMRI and plasma biomarker testing at baseline and week 24. MRI eligibility will be assessed separately, and contraindications to MRI will exclude only participation in the imaging component. Because this sub-cohort is not powered for confirmatory mechanistic inference, all imaging and biomarker analyses will be treated as exploratory and hypothesis-generating.

The rs-fMRI acquisition and preprocessing framework will be locked in an imaging manual before the first imaging visit. The minimum MRI protocol will include high-resolution three-dimensional T1-weighted structural imaging and resting-state echo-planar functional imaging on a 3.0-T scanner, with scanner model, sequence parameters, head-motion monitoring, eyes-open or eyes-closed instruction, and acquisition duration recorded for reproducibility. Preprocessing will include discarding initial volumes, slice-timing correction when applicable, realignment, co-registration, normalization to standard space, spatial smoothing, nuisance regression, temporal filtering, and motion scrubbing. Participants with excessive motion, defined *a priori* using framewise-displacement and gross-motion thresholds, will be excluded from affected imaging analyses. ROI analyses will focus on standard atlas-defined DMN and CEN regions, including posterior cingulate/precuneus, medial prefrontal cortex, lateral parietal cortex, dorsolateral prefrontal cortex, and posterior parietal executive-control regions. Whole-brain exploratory analyses may be conducted using appropriate correction for multiple comparisons.

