### Sample size

The planned sample size is 126 randomized participants, with 63 participants in each group. The calculation is based on the primary endpoint, defined as change in MoCA score from baseline to week 24. The assumed between-group difference of 1.6 MoCA points and common standard deviation of 3.0 points were selected as a plausible intervention effect for trial planning, informed by prior computerized or multi-domain cognitive training trials and reviews in older adults with cognitive impairment (5, 23, 24). This assumption is used for sample-size estimation only and is not presented as a universal minimal clinically important difference. The study is designed to test whether the intervention can detect a plausible efficacy signal within a feasible single-center protocol, rather than to establish a definitive clinically important difference threshold. With a two-sided alpha level of 0.05 and 80% statistical power, 56 participants per group are required. Allowing for approximately 10% attrition, the target sample size is inflated to 63 participants per group, yielding a total sample size of 126 participants.

Sensitivity calculations using the same alpha, power, and standard deviation assumptions indicate that detectable between-group MoCA differences of 1.0, 1.2, 1.4, 1.6, 1.8, and 2.0 points would require approximately 142, 99, 73, 56, 44, and 36 participants per group before attrition, respectively; after allowing for 10% attrition, the corresponding targets are approximately 158, 110, 82, 63, 49, and 40 participants per group. The nested imaging-biomarker sub-cohort target of approximately 25 participants per group is feasibility-based and will be used for exploratory estimates of effect direction, variance, and brain-behavior associations rather than confirmatory hypothesis testing.

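### The rs-fMRI plan compares connectivity change between groups and names no baseline connectivity term; stating one would tighten an exploratory estimate at about 25 per arm at almost no cost

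*Protocol article*

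**What the plan says.** The Protocol article, under Statistical analysis, describes the region-of-interest analysis in one sentence: "ROI-to-ROI connectivity changes will be analyzed using within-group and between-group models". The analyzed quantity is change, and the sentence names no covariate.

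The only covariate list in that section stands in the paragraph on the primary MoCA model: "Age, sex, education level, and baseline cognitive severity will be included as covariates when prespecified". It contains no connectivity term.

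Under Neuroimaging and biomarker sub-cohort, participants "will undergo rs-fMRI and plasma biomarker testing at baseline and week 24", so anyone with a change score also has a baseline value. The size is given as "A nested exploratory imaging-biomarker sub-cohort of approximately 50 participants (target 25 per group), subject to MRI eligibility, consent, and feasibility". Participants with too much head motion "will be excluded from affected imaging analyses", so the number analyzed may be smaller. That section also says that "all imaging and biomarker analyses will be treated as exploratory and hypothesis-generating". Under Sample size, the target of about 25 per group "will be used for exploratory estimates of effect direction, variance, and brain-behavior associations rather than confirmatory hypothesis testing".

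A separate statistical analysis plan is to be finalized before database lock. It is not shown.

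**The concern.** With one scan before and one after treatment, there are two common ways to estimate the group effect. One compares mean change between the arms. The other compares week-24 values, or change, with the baseline value as a covariate. Both are valid under randomization, but the first fixes the coefficient on baseline at 1 whatever the data show. When the within-person correlation is moderate or low, that over-corrects for baseline and adds variance.

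The sub-cohort exists to give estimates of direction, variance and association, and the plan puts its emphasis on effect sizes and confidence intervals. Precision is therefore the main product of this component, and about 25 per arm leaves little to spare. An analysis plan that took the sentence literally would adopt the less efficient estimator although the baseline value is already in hand.

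**Working it through.** **The plan's own figures.** No figure is given for the connectivity analysis; its 25 per group is based on feasibility. The one formal calculation, for MoCA, reproduces: 2 × (1.96 + 0.8416)² × (3.0/1.6)² = 55.2, rounded up to 56 per group, and 56/0.9 = 62.2, rounded up to 63. It has no bearing on the imaging models.

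**Inputs.**
- From the document: 25 per arm; scans at baseline and week 24.
- Assumed, because the document gives neither: equal variance at the two visits (set to 1), and a baseline-to-week-24 correlation ρ of 0.3 to 0.9.

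**Formulas.**
- Per-person variance, unadjusted change: 2(1 − ρ).
- Per-person variance, adjusted for baseline: 1 − ρ².
- Ratio, adjusted to unadjusted: (1 − ρ²) / [2(1 − ρ)] = (1 + ρ)/2.
- Standard error of the group difference: √(variance × 2/25).
- Relative interval width: the square root of the ratio.

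| ρ | Variance, change | Variance, adjusted | Ratio | Variance cut | SE, change | SE, adjusted | Interval narrower by |
|---|---|---|---|---|---|---|---|
| 0.3 | 1.40 | 0.91 | 0.65 | 35% | 0.335 | 0.270 | 19% |
| 0.5 | 1.00 | 0.75 | 0.75 | 25% | 0.283 | 0.245 | 13% |
| 0.7 | 0.60 | 0.51 | 0.85 | 15% | 0.219 | 0.202 | 8% |
| 0.9 | 0.20 | 0.19 | 0.95 | 5% | 0.126 | 0.123 | 3% |

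Standard errors are in units of the one-visit standard deviation of connectivity. To match 25 per arm with adjustment, unadjusted change would need 25 divided by the ratio: about 38, 33, 29 and 26 per arm.

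**Cost of estimating the slope.** At this size it adds about 2% to the adjusted variance. The ratios become 0.65 × 1.02 = 0.66, 0.75 × 1.02 = 0.77, 0.85 × 1.02 = 0.87 and 0.95 × 1.02 = 0.97. The gain at ρ = 0.9 all but disappears; the others barely move.

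**If the variances differ.** With standard deviations s₀ at baseline and s₁ at week 24, change has variance s₀² + s₁² − 2ρs₀s₁ and the adjusted analysis s₁²(1 − ρ²). The difference is (s₀ − ρs₁)², which is never negative. Apart from the slope cost, the direction of the result does not rest on equal variances; the percentages do.

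**Chance baseline differences.** At 25 per arm, the baseline difference between the arms has standard deviation √(2/25) = 0.283. A difference of that size moves the change contrast the opposite way by (1 − ρ) × 0.283, which is 0.20, 0.14, 0.08 and 0.03 at the four correlations. This is not extra to the table, because 2(1 − ρ) = (1 − ρ²) + (1 − ρ)² and the last term is exactly the variance of that shift. At ρ = 0.5, the squared standard errors are 0.080 and 0.060; their difference of 0.020 is 0.141².

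**The case against.** The strongest reply is that the sentence does not commit to an unadjusted comparison. A reader might infer that raw change will be analyzed with baseline connectivity left out. The document does not say so. It uses no word such as raw or unadjusted, and a between-group model of change may carry the baseline value. With it, the group coefficient is identical to that from regressing the week-24 value on group and baseline; only the slope on baseline differs, by 1. The section also lists standardized coefficients and partial eta-squared among its effect measures, and these sit naturally with regression models. All of this stands.

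Covariates of an exploratory imaging model are also commonly left to the analysis plan, which is not shown. The lack of a list is therefore not an error. What remains is that the article does fix change as the quantity compared, and the one list it gives, for MoCA, would not supply the missing term.

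Two further stronger readings fail:
- A reader might infer that change scores bias the result or leave imbalance uncorrected. Over randomization the change contrast is unbiased. It over-corrects in a given sample, and that shift is already counted in the variance. It could alter the sign of a small estimate, but so could any sampling error of that size.
- A reader might blame the lack of stratification by sub-cohort membership. Such stratification would balance numbers per arm, not connectivity values.

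Finally, the document itself says that the sub-cohort is not powered for confirmatory inference. That is why the size is expressed here as variance and interval width, and not as power.

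**Conclusion.** The point holds as a small, optional improvement. The text sets connectivity change as the outcome of the between-group models and neither names nor excludes a baseline connectivity term. If it is followed literally, the estimate is valid but less precise than it could be. Adjustment would cut its variance by about 35%, 25%, 15% or 5% at an assumed correlation of 0.3, 0.5, 0.7 or 0.9.

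These figures rest on equal variances at the two visits, on correlations that the document does not give, and on the full 25 per arm yielding usable scans at both visits for the standard errors. Motion exclusions would widen both intervals but leave the ratio unchanged. Nothing here is a contradiction or a wrong figure in the plan, and the consequence is confined to an exploratory analysis.

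**What to change.** Add one sentence to the rs-fMRI paragraph, or to the analysis plan before it is finalized: for each DMN/CEN region pair, the between-group effect is estimated by regressing week-24 connectivity (or, equivalently, its change) on group and the same pair's baseline connectivity, and reported with a 95% confidence interval.

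The cost is one degree of freedom per model. No new scans or participants are needed, and the article reports that recruitment has not begun, so the wording can be settled before any imaging data exist.

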### Ethics and dissemination

This study has been reviewed and approved by the Ethical Committee of the School of Nursing and Rehabilitation, Shandong University (Approval No. 2026-R-072; approved March 10, 2026). The trial has also been prospectively registered with the Chinese Clinical Trial Registry (ChiCTR2600125870). The trial will be conducted in accordance with the Declaration of Helsinki, relevant national ethical requirements, and institutional data protection policies. Written informed consent will be obtained before enrollment.

Participants will be informed of the study purpose, procedures, potential benefits and risks, confidentiality protections, voluntary nature of participation, and the right to withdraw at any time without affecting usual services. The main foreseeable risks are fatigue, frustration, transient emotional discomfort during cognitive tasks, privacy concerns related to digital interaction data, and MRI- or venipuncture-related discomfort in the exploratory imaging-biomarker sub-cohort. These risks will be mitigated through trained facilitators, real-time stop rules, privacy safeguards, and adverse-event monitoring.

Findings will be disseminated through peer-reviewed publication, conference presentation, and reports to relevant clinical and community stakeholders. Results will be reported regardless of the direction or magnitude of findings. Trial registry information will be kept current throughout the study.

## Discussion

This protocol describes an adaptive cognitive training intervention that integrates embodied social interaction, LLM-supported dialogue, and JITAI-based state tailoring for older adults with MCI. The design addresses a key limitation of many existing digital cognitive interventions: the inability to respond to momentary cognitive load, frustration, fatigue, or disengagement. By using a socially assistive robot as the interaction interface, the intervention aims to make cognitive training more socially meaningful and ecologically acceptable for older adults.

A major methodological contribution is the explicit separation of adaptive mechanisms from general cognitive stimulation. The active control condition is matched on training frequency, session duration, facilitator attention, visit environment, and cognitive domains, while withholding real-time state monitoring, rule-based tailoring, bounded LLM communication, embodied robot social behaviors, and affective-motivational tailoring. This comparison should help estimate the added value of adaptive embodied interaction beyond non-specific exposure to digital training, although expectancy, novelty, and perceived social presence may still differ between groups and will be measured to support interpretation.

The protocol also incorporates AI-specific governance elements. LLM versioning, prompt standardization, safety filters, constrained output categories, latency fallback rules, human oversight, transcript audit, and error-case review are intended to improve transparency and reproducibility. These procedures are essential because LLM-based systems can generate plausible but inaccurate or inappropriate content if not constrained and monitored. In this trial, the LLM is therefore treated as a bounded intervention component rather than an autonomous clinical decision-maker.

The nested imaging and biomarker sub-cohort may provide exploratory evidence about possible neurobiological correlates of adaptive cognitive training. Changes in DMN and CEN connectivity may help evaluate whether behavioral improvements are accompanied by altered network organization. Plasma BDNF, p-tau181, and NfL may provide complementary information about synaptic plasticity and neurodegeneration-related processes, although biomarker changes over a 24-week period should be interpreted cautiously.

Several limitations should be acknowledged. The single-center design may limit generalizability. Participants and facilitators cannot be blinded, and the AI-Robot intervention may differ from the control condition in social engagement, novelty, expectancy, and perceived human-likeness despite matching for dose and facilitator contact. The imaging-biomarker sub-cohort may be underpowered for small neurobiological effects. The LLM module introduces risks of technical failure, inappropriate output, prompt sensitivity, hidden bias in generated responses, reproducibility challenges across model versions, language- and culture-specific generalizability constraints, and model drift; these risks are mitigated through version control, locked prompts, safety constraints, latency fallback, audit procedures, and human supervision. Because the study is not yet recruiting, careful site preparation, facilitator training, registry updating, and intervention-manual locking will be important for ensuring protocol fidelity before enrollment begins.

In conclusion, this study will evaluate whether an LLM-supported socially assistive robot can deliver adaptive, affect-sensitive cognitive training for older adults with MCI. If effective, the approach may inform the development of scalable, personalized digital therapeutics that combine cognitive rehabilitation, human-robot interaction, and responsible AI governance.
